#### Interventions

##### Control group

Reflective of current UK practice [7], after surgery, the patient’s shoulder will be immobilised using a sling for 4 weeks. They will have one session in the hospital with a physiotherapist, after surgery but prior to discharge. This session will include advice to maintain the sling in situ at all times. It should be removed *only* to perform specific daily exercises (table slides, active elbow, wrist and hand exercises and passive shoulder abduction, flexion and lateral rotation movements, within pain limits), or for eating, washing and dressing. The sling should also be worn at night. No further active movement will be encouraged. A post-operative information and exercise booklet with photographs and text detailing the exercise type and number of sets and repetitions will be provided. This initial discussion will be followed up approximately 2 weeks later at an outpatient appointment with the physiotherapist, who will reconfirm this advice.

Adherence to the programme, i.e. time out of the sling, will be measured using a personal exercise diary. This was developed in association with our patient and public involvement and engagement (PPIE) group and will be provided by the physiotherapist. Participants will be asked to record in the diary for how long they were not wearing the sling at regular periods throughout the day, in the same way as the intervention group. Participants will also be asked to record the extent to which they feel they have adhered to the prescribed exercise plan.

##### Intervention group

The intervention group will undergo early patient-directed rehabilitation. This includes one session in hospital with a physiotherapist, after surgery but prior to discharge. In contrast to the control intervention, this session will include advice to remove the post-operative sling, as pain allows, as soon as possible and gradually to begin actively using the arm within the limits of their pain. This use will increase over time according to agreed goals within the context of the patient’s own pain experience and tolerance. Like the participants in the control group, participants in the intervention group will also receive advice to perform specific daily exercises (table slides, active elbow, wrist and hand exercises, and passive shoulder abduction and flexion movements, all within pain limits). However, given that the intention of the intervention is to encourage early movement after surgery, if participants remove their arm from the sling at times other than to exercise, then they will not need to do the basic table slides and active elbow, wrist and hand exercises. Instead, they will be advised that only shoulder abduction, flexion and lateral rotation movements are required to encourage range of movement. A post-operative information and exercise booklet with photographs and text detailing the exercise type and number of sets and repetitions will be provided.

This initial discussion will be followed up approximately 2 weeks later at an outpatient appointment with a physiotherapist to discuss progress, address barriers to sling removal and active functional shoulder movement, and to facilitate adherence with the early rehabilitation. As with the control group, an assessment of the implementation of and adherence to the intervention will be facilitated by the personal exercise diary, which the participant will use to record the time out of the sling at regular periods throughout the day. Participants will also be asked to record the extent to which they feel they have adhered to the prescribed exercise plan.

##### Both groups

Both groups will be provided with the same type of sling and advised to take pain medication as prescribed. Use of medication will be self-reported and analysed. After 4 weeks, both groups will commence 1:1 physiotherapy as per current UK practice, which includes a progressive exercise programme targeting range of movement, strength and function [7] as follows:Phase 1: Progress to assisted movement (shoulder movement with assistance) then full active movement (shoulder movement by the patient) within pain limitsPhase 2: Isometric exercises (resisted static exercises) for all shoulder muscle groupsPhase 3: Resisted exercises through range, within limits of painPhase 4: Functional restoration

This physiotherapy protocol has been agreed with all clinical sites. Progress between the phases will be individualised and guided by the patients’ acceptable symptom response over four further physiotherapy sessions (six in total) complemented by a home exercise programme. Delivery of the intervention and control treatments will be supported by a manual for the physiotherapists.

#### Study training

Research health-care practitioners will be trained in each of the participating centres on the participant eligibility criteria, the approach to recruitment and consent, the requirements for the completion of all study paperwork, good clinical practice as applicable to research and the maintenance of the study site file and study records. Reporting of serious adverse events and adverse events will also be covered.

In addition, the clinical physiotherapists, both those who will initially prescribe the study intervention to patients on a ward in an in-patient setting and those who will subsequently assess and treat patients in an outpatient setting, will be trained prior to the start of recruitment and treatment. Due to the limited number of clinical physiotherapists within the clinical site teams, each clinical physiotherapist will treat patients in both arms. However, given the protocolised nature of the interventions, we do not expect a significant contamination effect and we will include contamination and how to avoid it within the study training.

The focus of this training will be on delivery of the interventions and will be supplemented by a comprehensive manual providing clear treatment protocols and guidance on study paperwork for the clinicians. They will also receive instruction sheets for the exercises, personal exercise diaries for participants and post-operative patient information booklets with information on returning to usual activities, including driving and work. The training will take the form of workshops consisting of information provision, question and answer sessions and role play with regards to supporting the approach to early patient-directed rehabilitation and overcoming any barriers.

The sonographers will undertake the USS of the shoulder at 12-weeks to assess whether the RC has re-torn. The USS will be focused on the RC and details of the RC tear and surgery will be provided, as described above. The sonographers will be provided with information regarding the RaCeR study and will be offered the opportunity to discuss the protocol with the research team. However, because the protocol reflects usual practice in the UK, further formal training will not be routinely offered.

### Outcomes

#### Feasibility outcomes

Numbers of potentially eligible and eligible patients, number invited, number attending a pre-operative assessment clinic and consent rates (target recruitment is six or seven participants per month over a 12-month recruitment period)Number of eligible patients found subsequently during surgery not to have an RC tear (indicating a false positive scan)Feasibility of recruiting participating centres and number of additional centres in which staff are interested in participating in a future main trialRate of retention in the trial, including response rates to questionnaires and individual measures (including resource use) and SMS text messagesIntervention fidelity and adherence using physiotherapist-completed case report forms and patient-completed personal exercise diaries for time out of slingDetermining the primary outcome measure for the main trial by assessing and comparing sensitivity to change of the measures and other statistical properties to support sample size derivation, comparing follow-up rates of different methods of data capture (questionnaire/SMS text) and of individual measures, and evaluating which outcome measures best reflect the patients' rehabilitation goals, identified from the qualitative interviews,Participant satisfaction with the interventions on a five-point ordinal scale, ranging from very satisfied, satisfied, neutral and dissatisfied to very dissatisfiedPatient and clinician views about the acceptability of the interventions (qualitative data)

#### Clinical outcomes

Pain and disability assessed using the OSS and SPADI at baseline, 6 weeks post-surgery by post and 12 weeks post-surgery in person during a follow-up clinic visit or by postal questionnaire, or by telephone call to collect minimal data if there is no response to the postal questionnaireHealth-related quality of life assessed using the EQ-5D-5L at baseline, 6 weeks post-surgery by post and 12 weeks post-surgery in person during a follow-up clinic visit or by postal questionnaireGlobal change question at 6 weeks post-surgery by post and 12 weeks post-surgery in person during a follow-up clinic visit or by postal questionnaire, or by telephone call to collect minimal data if there is no response to the postal questionnairePain in the last week (derived from the OSS) using weekly SMS text messages for 12 weeks post-surgery based on a 0–4 numerical rating scale with anchors of *no pain* (0) to *unbearable pain* (4)Disability relating to work or activity interference due to the shoulder problem in the last week (derived from the OSS) using weekly SMS text messages for 12 weeks post-surgery based on a 0–4 numerical rating scale with anchors of *not at all* (0) to *totally* (4)Days lost from work due to the shoulder problem at 6 weeks post-surgery via postal questionnaire and 12 weeks post-surgery via questionnaire completed during a follow-up clinic visitTime taken to return to driving, if applicable, via a questionnaire at the 6- and 12-week follow-upsNumber and type of adverse events, e.g. post-procedural exacerbation of pain, for up to 12 weeks post-randomisation via patient self-report questionnaire at 6 and 12 weeks post-surgery and via surgeon, physiotherapist or general practitioner reportDiagnostic USS performed by a sonographer independent of the study to assess the integrity of surgical repair at 12 weeks post-surgery

We will also collect self-report data relating to further health-care resource use, including NHS- and private-borne service and medication costs as well as data from the surgery itself, including the completeness of the surgical repair, and questions relating to the patient’s occupation and their loss or gain of productivity at work.

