### Objectives

The objectives of this pilot and feasibility RCT are as follows:To determine the availability of eligible patients and the rate of recruitment.To determine the rate of retention and the response rates to questionnaires and SMS text messages.To determine whether the interventions can be delivered per protocol, including an assessment of adherence, i.e. the time out of sling for both the early rehabilitation group and the sling immobilisation group.Determine the primary outcome measure for the main trial by evaluating sensitivity to change and assess other statistical properties related to clinical outcomes (e.g. standard deviation, betweenmeasurement correlations, event rate) that would be required to inform the sample size calculation for a main trial as well as an assessment of the completeness of follow-up between different methods of data capture (questionnaire and SMS text),Determine rate of response and completion of healthcare resource use questionnaire and productivity, including return to work,Explore participant satisfaction with interventions,Determine rate of tendon re-tear or failed healing (same outcome that RC is not intact) at 12-weeks post-surgery determined via diagnostic ultrasound,Determine number and nature of adverse events via self-report questionnaire.

Semi-structured qualitative interviews will be undertaken:To determine the acceptability of the interventions to patients and clinicians.To identify the barriers and enablers to adherence.To identify which outcome measures best reflects the participants’ rehabilitation goals.

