### Study setting

Patients will be recruited from orthopaedic departments of the participating UK NHS hospitals. Following surgery to repair the RC, the study interventions will be delivered prior to discharge while the patient is on the hospital ward. Subsequent components of the study interventions will be delivered through outpatient physiotherapy settings in, or affiliated to, the main hospitals.

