During the telephone call, medical note review and face-to-face meeting, the patient’s age and year of birth, gender, diagnosis, size and location of RC tear and, if applicable, reason for exclusion will be collected. Once patients have been identified, and it is confirmed that they have a symptomatic RC tear and are 18 years or older, the research health-care practitioner will check their medical notes to confirm that the surgeon responsible for their care does not wish them to be excluded from participation in the study prior to contacting them. This checking process will be documented.

Interested and eligible patients will be required to provide written informed consent before participating. Typically, written informed consent will be sought at the time of the pre-operative assessment or other convenient time prior to surgery. A research health-care practitioner, who will have received appropriate training and is authorised on the trial delegation log, will take informed consent. A record of the consent process will be kept in the patient’s medical records. The original consent form will be retained in the study site file and a copy will be given to the participant. A copy will also be securely sent to Keele Clinical Trials Unit (CTU) for monitoring purposes.

Participants have the right to withdraw at any time without any consequence to any future care they may require. For each trial participant, their general practitioner will be sent a letter from Keele CTU to confirm that their patient is taking part in the research study.

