### Data collection

The research health-care practitioner will provide the baseline questionnaire to consenting patients for them to complete themselves. This collects demographic data, general practitioner details, the Oxford Shoulder Score (OSS), the Shoulder Pain and Disability Index (SPADI) and EQ-5D-5L. The patient will be given adequate time and a suitable location to complete the baseline questionnaire. It will be checked for completeness by the research health-care practitioner. The original baseline questionnaire will be sent to Keele CTU and a copy retained in the study site file. Once the baseline questionnaire has been completed and checked, the participant will be randomised to either the intervention or control group.

The size and location of the tear will be recorded, since these may be important determinants of the clinical outcome. This information will be collected by the research health-care practitioner from the pre-operative imaging, ultrasound scan (USS) or MRI, which will typically be available in the medical notes. Due to concerns about the reliability of measurements of the size and location of a tear by imaging alone, the physiotherapist who delivers the allocated treatment will record the intra-operative findings of the size and location of the tear and the completeness of repair as they will typically have access to this information. The completeness of the repair will allow the study team to contextualise the USS 12 weeks post-operatively. Previous studies have been criticised for reporting re-tears only dichotomously, i.e. torn or not, whereas a re-tear identified on an USS might just reflect that the tear was only partially repaired or not repaired at the time of the operation.

The OSS is a 12-item shoulder-specific self-report measure of shoulder pain and function, primarily used to assess the outcome of shoulder surgery in RCTs [21]. The OSS is reliable, valid, responsive and acceptable to patients [21–23]. The items refer to the past 4 weeks. Each has five ordinal response options scored from 0 to 4, with 4 representing the best outcome. When the 12 items are summed, this produces an overall score ranging from 0 to 48, with 48 being the best outcome.

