### Blinding

The participant will be informed of the allocation only by the physiotherapist who will deliver the allocated treatment, and the surgeon will remain unaware of the allocation until after the surgery to minimise the likelihood of withdrawal through knowledge of the allocated intervention. No further measures to blind participants, clinicians, research team or oversight committees will be implemented in this external pilot and feasibility RCT.

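### The adverse-event window ends 12 weeks after randomisation, but randomisation precedes surgery and the collecting questionnaires are timed from surgery: a minor correction to one sentence

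*Protocol article*

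**What the plan says.** In the protocol article, the Clinical outcomes section has adverse events recorded "for up to 12 weeks post-randomisation via patient self-report questionnaire at 6 and 12 weeks post-surgery", and also through reports from the surgeon, physiotherapist or general practitioner. The outcome serves a stated objective: "Determine number and nature of adverse events via self-report questionnaire".

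The order of events has to be pieced together from several sections:

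- Recruitment: typically, "written informed consent will be sought at the time of the pre-operative assessment or other convenient time prior to surgery".
- Data collection: "Once the baseline questionnaire has been completed and checked, the participant will be randomised to either the intervention or control group". The randomisation scheme section repeats that consent and a completed baseline questionnaire come first, and has the allocation left in an envelope or electronic note for the treating physiotherapist.
- Blinding: "the surgeon will remain unaware of the allocation until after the surgery to minimise the likelihood of withdrawal through knowledge of the allocated intervention".
- Study setting: "Following surgery to repair the RC, the study interventions will be delivered prior to discharge while the patient is on the hospital ward".

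No other item in the Clinical outcomes list has a period counted from randomisation. The ultrasound scan, for example, is "to assess the integrity of surgical repair at 12 weeks post-surgery".

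**The concern.** The definition gives an end point on one clock and collection times on another. If randomisation comes before surgery, the window closes before the second of the two questionnaires named in the same sentence. An analyst then has two readings to choose between: count every event reported at the 12-week questionnaire, or only those dated within 12 weeks of randomisation. The text supports both.

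Reports from surgeons, physiotherapists and general practitioners are more exposed. They have no visit time of their own, and the only end date the sentence gives them is the one counted from randomisation. A site that follows the wording could stop reporting while patients are still inside their 12 post-operative weeks.

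At stake is the absolute event rate, which a pilot trial should hand on to the main trial with a clear denominator. A window that ends at a different post-operative time for each patient does not provide one. It may also take in events before surgery, which cannot result from rehabilitation that has not begun.

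**Working it through.** There is no power or precision figure to reproduce here. The check is a reading of the timeline followed by simple arithmetic.

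**Step 1: does randomisation precede surgery?** No single sentence says so, but it follows from the sections taken together. Consent is sought before surgery. Randomisation follows once the baseline questionnaire has been completed and checked. An allocation that is kept from the surgeon until after the operation must already exist at the operation. The randomised treatments then start on the ward, after surgery.

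**Step 2: how long is the interval?** The article does not say. Consent may be taken at the pre-operative assessment or at another time before surgery, and no minimum, maximum or fixed wait is given. The interval g, in weeks, is therefore an assumption, shown as a range.

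**Step 3: where does the window close?** Surgery takes place g weeks after randomisation, so:

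- post-operative week at which the window ends = 12 - g
- share of the 12 post-operative weeks covered = (12 - g) / 12
- time from the window's end to the 12-week post-surgery questionnaire = 12 - (12 - g) = g weeks

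| Assumed wait g (weeks) | Window ends at post-operative week | Share of 12 weeks covered | 6-week questionnaire inside? | 12-week questionnaire inside? |
|---|---|---|---|---|
| 0 | 12 | 100% | yes | yes |
| 1 | 11 | 92% | yes | no |
| 2 | 10 | 83% | yes | no |
| 4 | 8 | 67% | yes | no |
| 6 | 6 | 50% | yes, at the limit | no |
| 8 | 4 | 33% | no | no |

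The two time points agree only at g = 0. That the 12-week questionnaire falls outside the window for any g above zero does not depend on the assumed values; the percentages do.

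**Step 4: which weeks drop out?** They are the last g weeks before post-operative week 12. Under the Interventions section the two arms differ mainly in the first 4 weeks, after which both start the same physiotherapy. The first 4 weeks stay inside the window as long as 12 - g is at least 4, that is, for waits of up to 8 weeks. What is at risk is late-reported or late-emerging events, not the period of greatest contrast.

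**Step 5: what if the window is anchored to surgery?** It then covers 12 of 12 post-operative weeks for every patient and includes both questionnaires, whatever g is.

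**The case against.** The strongest reply is that this is a slip of wording with little practical effect. The objective is framed around self-report, and the questionnaires are fixed at 6 and 12 weeks after surgery whatever the wait. Patients will be asked about late events in any case, and such events are lost only if someone later discards them by date, which the article does not instruct. This largely stands for the questionnaire route. It does not rescue reports from surgeons, physiotherapists and general practitioners, and it leaves the analyst without a rule.

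A reader might infer that the comparison between arms is biased, or that rates cannot be compared. The documents do not support this. Allocation is 1:1 and blocked by site, participants learn it only from the treating physiotherapist, and the surgeon does not know it until after the operation. The wait should therefore not depend on the arm. Unequal time at risk between patients is a problem for absolute rates, not a source of systematic difference between groups.

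A reader might also infer that the main safety question is compromised. The Discussion names re-tear as the principal concern about early rehabilitation, and re-tear has its own objective and a scan timed from surgery. Nor do adverse events enter any of the three success criteria, which concern recruitment, time out of sling and follow-up.

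Two further limits stand. The sentence gives only an end point, so the counting of pre-operative events is an inference. The full protocol (version 2.0) is not shown and may word the rule differently.

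**Conclusion.** The contradiction is real and lies in the current text. It is not a detail left to an analysis plan. Whenever randomisation precedes surgery, the stated window closes before one of its own collection points, by exactly the length of the wait.

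The size of the loss cannot be determined from the article. Coverage of 10, 8 or 6 of the 12 post-operative weeks rests on assumed waits of 2, 4 or 6 weeks, and shorter waits are possible. That the wait varies between patients is also an inference, though a natural one, since consent can be taken at different times and no interval is fixed.

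The likely harm is some undercounting of absolute post-operative event rates, chiefly through clinician and general practitioner reports, together with unequal time at risk between patients. No bias between arms, loss of the re-tear outcome or effect on the decision to proceed to a main trial follows. This is a minor correction and not one on which the trial's validity depends.

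**What to change.** Reconcile the two time origins in the Clinical outcomes section. End the adverse-event window at 12 weeks after surgery for all sources (patient questionnaire, surgeon, physiotherapist and general practitioner), in line with the other timed outcomes in that list. Report any events between randomisation and surgery separately as pre-treatment, so that they are kept but do not enter the post-operative rates.

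The cost is one corrected sentence, carried into the analysis plan. If the full protocol or the site training material has the same wording, sites should also receive a short notice. No new visit, questionnaire or data item is needed, because both post-surgery questionnaires are already planned.
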